### Process measures

Process data will be collected during the intervention at the active intervention hospitals, with the objective of allowing for early detection and correction of implementation problems. This will allow detection of implementation problems if the intervention is not effective or facilitation of the intervention if it is effective. Three categories of process measures will be considered: program inputs, guideline implementation activities, and birth attendants' reactions.

### Data collection

Although the hospital will be the unit of analysis, we shall collect individual patient data in order to assure data quality. The goal is to accumulate data on approximately 300–500 deliveries from each hospital. All the hospitals in the project use a standard perinatal clinical record form (PIS form) [33]. This form includes the data of the obstetric history, prenatal care, labor, delivery, and neonatal outcomes. To obtain the additional necessary data to calculate the outcome variables, we will implement a modified version of the PIS clinical record that will add some variables at the bottom of the form to be addressed during the data collection periods. This approach will reduce to a minimum extra activities associated with data collection by the birth attendants during the study.

Blood loss during the third stage of labor (after delivery) will be measured from all vaginal deliveries during the data collection periods. A plastic, transparent, collection drape will be employed. At the end of the blood collection period, the amount of blood loss will be measured by pouring the contents of the drape into a calibrated pitcher. The amount of blood loss will be recorded in the data form together with the time (beginning and end) of the blood collection.

To measure provider's readiness to change, a self-administered questionnaire was designed and will be completed by all physicians and midwives at all participating hospitals, before randomization and at the end of the intervention.

### Data management

The data collection system to determine outcomes will be independent from the implementation of the intervention. Given the nature of the intervention, we cannot blind the randomization, and data collectors will likely know if they are part of an intervention/control hospital. In addition, intervention hospitals will monitor and record clinical data (i.e., episiotomy rate and active management of the third stage of labor) through their routine data collection system. As a consequence, it is expected that the proposed intervention will improve the capacity of intervention hospitals to collect and review clinical data with the potential of introducing bias in the outcome assessment. To minimize this bias, the data collection system will as much as possible be isolated from the intervention instruments.. In practical terms, this means that data collectors at the hospital level, the data supervisors and the associated computer software used for data collection will not be associated with intervention activities.

Each participating hospital will receive a computer with an Internet access to be used for data collection purposes. A custom developed data management software program will be installed in each computer and will be used by trained and certified in-hospital data collectors, for distributed data entry, data validation and data transmission to the coordinating unit. The system provides a secure environment for confidential medical information and the access to it will be limited to authorized individuals. No personal identifiers will be transmitted from the hospital to the data coordinating unit

### Sample size

The sample size was estimated based upon the hospital being the unit of analysis. A preliminary analysis of data from Argentinean hospitals [2] documented a baseline frequency of episiotomies in vaginal deliveries of 42%, with a standard deviation of 11%. To protect against changes in the standard deviation [15], we have based our calculations on a standard deviation of 15%. Thus, we need 18 hospitals (9 intervention and 9 control) to identify a decrease of episiotomy rates from 40% to 20%, with a 0.05 significance level and 80% power. Considering that in public hospitals in Argentina and Uruguay about 25% of deliveries are seen among primiparae, and 75% among multiparae, a reduction of the general episiotomy rate from 40% to 20% could be achieved by reducing the rate among primiparae from 80% to 40%, and the rate among multiparae from 26% to 13%. The rates after this intervention would thus be similar to the rates achieved in a previous trial [34] and are therefore potentially attainable. Moreover, the sample size of 18 hospitals will allow identification of smaller decreases of episiotomy rates among primiparae vaginal deliveries, from 80% to 60%, with a 0.05 significance level and 80% power.

We expect the use of oxytocin during the third stage of labor to increase from 10% to 50%. However, assuming a baseline frequency of oxytocin use of 10% and a standard deviation of 5%, a sample size of 18 hospitals will provide a power > 95% to identify an increase in oxytocin use from 10% to 20%, with a 0.05 significance level. Assuming a baseline incidence rate of post-partum hemorrhage of 15% and a standard deviation of 5%, a sample size of 18 hospitals will provide a power of 84% to identify a reduction in hemorrhage from 15% to 8%.

Hospitals will initiate baseline data collection to obtain information that will be used to assess the inclusion criteria before randomization. A total of 24 hospitals were included to allow for hospital drop-outs.

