### Data analysis

Inference will be primaryly directed at the cluster (hospital) level. All analyses addressing the study research questions will use the "intention to treat" principle, comparing the outcome in the intervention group to the nonintervention group.

The outcome variables will be the percentage of primary and secondary outcomes measured during the three months following the end of the intervention. Mantel Haenszel summary risk ratios combining the individual ratios for each hospital in the intervention group and non-intervention group will be computed. The intervention and non-intervention groups will then be compared at the group level using Student's t-test on the logarithms of the summary risk ratio [17].

In addition, the data collected at the individual level will be used to explore the potential for confounding of the main effects of the intervention due to imbalances arising from the group randomization. Such multi-level analyses will use mixed model techniques (hierarchical linear models) [35,36].

For the analysis of provider's "readiness to change," the data will be summarized in terms of medians and interquartile ranges. Non-parametric statistics will be used to compare the pre- and post-intervention differences between the control and intervention groups.

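### The 18 hospitals said to give 80% power for episiotomy come from the large-sample normal formula; a t-test on the same hospital percentages has 76% power, or 78% with the 19 hospitals to be randomised

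*Protocol article*

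**What the plan says.** All references are to the protocol article.

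- **Sample size, unit:** "The sample size was estimated based upon the hospital being the unit of analysis".
- **Sample size, SD:** preliminary Argentinean data "documented a baseline frequency of episiotomies in vaginal deliveries of 42%, with a standard deviation of 11" per cent. As protection against a change in that spread, "we have based our calculations on a standard deviation of 15" per cent.
- **Sample size, main claim:** "we need 18 hospitals (9 intervention and 9 control) to identify a decrease of episiotomy rates from 40% to 20" per cent, at the 0.05 level with 80% power. The section names neither the formula nor the sidedness.
- **Sample size, primiparae:** the same 18 hospitals "will allow identification of smaller decreases of episiotomy rates among primiparae vaginal deliveries, from 80% to 60" per cent, again "with a 0.05 significance level and 80% power". No separate SD is given.
- **Sample size, other outcomes:** with an SD of 5 points for each, 18 hospitals are said to give 84% power for postpartum hemorrhage from 15% to 8%, and more than 95% for oxytocin use from 10% to 20%.
- **Participating hospitals and Randomization procedures:** 19 hospitals will be randomised. The split between arms is not stated.
- **Data analysis:** the groups are compared "using Student's t-test", applied to logarithms of summary risk ratios.

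**The concern.** With 9 hospitals per arm, the t-test estimates the SD from 16 degrees of freedom, so its two-sided 5% critical value is 2.12 rather than 1.96. A sample size taken from the normal formula is then too small for the power claimed. In a large trial the difference is negligible; with 18 units it is not.

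This calculation sets the size of the trial for a primary outcome. It also affects how the loss from 24 hospitals to 19 is read. Against a requirement of 18, one hospital is to spare; against 20, the trial is one short.

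**Working it through.** **Inputs (Sample size section).** Difference 20 points (40% to 20%), SD 15 points, alpha 0.05, 9 v 9 hospitals. Two assumptions are mine: a two-sided test, because it reproduces the stated figures, and a 9 v 10 split of the 19 hospitals.

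**Step 1: reproduce the plan's figure.**

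- Normal formula: n per arm = 2 × (1.96 + 0.84)² × 15² / 20² = 8.8, rounded up to 9.
- Standard error at 9 v 9 = 15 × √(1/9 + 1/9) = 7.07. Standardised difference = 20 / 7.07 = 2.83.
- Normal power = Φ(2.83 − 1.96) = 80.7%. This matches the stated 80%.
- Check on hemorrhage: 7 / (5 × √(2/9)) = 2.97, and Φ(2.97 − 1.96) = 84.4%. This matches the stated 84%, so the same formula evidently lies behind both figures.
- A one-sided t-test at 9 v 9 would give 85.6% for episiotomy, which does not match.

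**Step 2: the same inputs under a two-sided t-test.** Power is the probability that a non-central t variable, with n₁ + n₂ − 2 degrees of freedom and non-centrality 20 / (15 × √(1/n₁ + 1/n₂)), falls beyond the critical value.

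| Hospitals | df | Critical t | Non-centrality | t-test power | Normal power |
|---|---|---|---|---|---|
| 9 v 9 | 16 | 2.12 | 2.83 | 75.7% | 80.7% |
| 9 v 10 | 17 | 2.11 | 2.90 | 78.1% | 82.7% |
| 10 v 10 | 18 | 2.10 | 2.98 | 80.5% | 84.6% |

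Simulation with 200,000 replicates gave 75.5% at 9 v 9 and 78.2% at 9 v 10. Solving instead for the difference detectable with 80% power at SD 15 gives 21.1 points (9 v 9) and 20.5 points (9 v 10).

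**Step 3: the other figures, t-test.**

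- Hemorrhage 15% to 8%, SD 5: 79.6% at 9 v 9 and 81.9% at 9 v 10, against the stated 84%.
- Primiparae 80% to 60%: also 20 points, so the results equal those in the table if the SD is 15.
- Oxytocin 10% to 20%, SD 5: 97.8% at 9 v 9. The claim of more than 95% stands.

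**Step 4: sensitivity to the SD.** At the observed SD of 11, t-test power for episiotomy is 95.1% (9 v 9) and 96.1% (9 v 10). The t-test reaches 80% once the SD is about 14.2 (9 v 9) or 14.6 (9 v 10).

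**Step 5: the log scale.** The article gives no log-scale SD, so these are illustrations only. Treat hospital rates as lognormal, with log variance log(1 + (SD/mean)²) in each arm, and average the two variances for the pooled SD.

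- SD 15 in both arms: pooled log SD 0.54. With a difference of log 2 = 0.69, power at 9 v 9 is about 73%. If the difference in mean logs is instead derived from the lognormal means, it is 0.85 and power is about 88%.
- SD halving with the mean (15 and 7.5): pooled log SD 0.36, difference 0.69, power about 97%.

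**The case against.** The strongest reply is that nothing was miscalculated. The normal formula is a standard approximation, the figures reproduce with it, and the section does not claim exact t-test power. That stands as an account of where the figure came from. It does not make 80% correct for a t-test with 16 degrees of freedom.

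Second, the SD of 15 is already a cautious value. This also stands: the whole gap equals moving the SD from 15 to about 14.2, or 14.6 with 19 hospitals, well inside the margin above the observed 11. But the 80% is stated for 15, so it should be true at 15.

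Third, the shortfall with 19 hospitals is only 1.9 points. That is correct. The article's claim, however, is about 18 hospitals, where the miss is more than four points.

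A reader might also go further and infer that 76% or 78% is the power of the planned primary analysis. The article does not support that. The planned t-test is on log summary risk ratios, no SD on that scale is given, and the illustrations above run from 73% to 97%. Nor does it support a firm statement on primiparae, for whom no SD is given. Finally, adjustment for baseline rates cannot be claimed to recover the loss, because that would need a baseline correlation the article does not report.

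**Conclusion.** The concern holds for the scale on which the trial was sized. With the article's own inputs, a two-sided t-test on hospital percentages has 76% power with 18 hospitals, a type II error of 24% instead of 20%, and 20 hospitals are needed for 80%. With the 19 to be randomised, power is 78%. Hemorrhage power with 18 hospitals is 80% rather than 84%; the oxytocin claim is unaffected.

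This rests on a two-sided test, equal SDs in the two arms, a 9 v 10 split for the 19 hospitals and, for primiparae, an SD of 15. Whether the planned log risk ratio analysis falls short of 80% cannot be settled from the article.

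Severity: moderate. The sizing statement is too favourable, but the shortfall with 19 hospitals is small, the SD was deliberately inflated, and no decision on design or allocation turns on it.

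**What to change.** In Sample size, replace the normal-formula figures by non-central t figures for the 19 hospitals (assuming 9 v 10):

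- **Episiotomy at SD 15:** 78% power for a 20-point fall, or 80% power for a 20.5-point fall.
- **Hemorrhage, 15% to 8% at SD 5:** about 82%.
- **Primiparae, 80% to 60%:** state the SD assumed; 78% applies if it is 15.

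State that the test is two-sided and that the figures apply to a t-test on hospital percentages. For episiotomy, add that the SD of 15 was deliberately raised from 11. Then either give power for the log risk ratio analysis with its assumed log-scale SD, or say plainly that the sizing was done on the percentage scale.

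This is a text change. No hospitals need be added, and the only cost is a slightly less favourable stated power.

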### Data analysis

Inference will be primaryly directed at the cluster (hospital) level. All analyses addressing the study research questions will use the "intention to treat" principle, comparing the outcome in the intervention group to the nonintervention group.

The outcome variables will be the percentage of primary and secondary outcomes measured during the three months following the end of the intervention. Mantel Haenszel summary risk ratios combining the individual ratios for each hospital in the intervention group and non-intervention group will be computed. The intervention and non-intervention groups will then be compared at the group level using Student's t-test on the logarithms of the summary risk ratio [17].

In addition, the data collected at the individual level will be used to explore the potential for confounding of the main effects of the intervention due to imbalances arising from the group randomization. Such multi-level analyses will use mixed model techniques (hierarchical linear models) [35,36].

For the analysis of provider's "readiness to change," the data will be summarized in terms of medians and interquartile ranges. Non-parametric statistics will be used to compare the pre- and post-intervention differences between the control and intervention groups.

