### Participating hospitals

Twenty four public hospitals in Argentina and Uruguay that had at least 1000 vaginal deliveries per year, and had no explicit policy for selective episiotomy or active management of third stage of labor were invited to participate. Those pre-selected hospitals that agreed to participate, collected baseline data. From the 24 hospitals, only 19 will be randomized because the analysis of their baseline data confirmed episiotomy rates in women with single vaginal births higher than 20%, and active management of the third stage of labor 25% or less.

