### Randomization procedures

Since only 19 hospitals will participate in the intervention trial, random allocation may not provide adequate balance in the groups regarding important prognostic variables [21]. We will use a minimization procedure to assure balance between intervention and control hospitals on five important prognostic variables: 1) baseline episiotomy and active management rates, 2) residency programs, 3) country (Argentina-Uruguay), 4) hospital size (number of births per year), and 5) region within the country. Minimization has the advantage that it can match small numbers of similar units with respect to several unit characteristics [22], and may be considered methodologically equivalent to randomization [23].

Because all hospitals will enter the study at the same time, all prognostic variables are known in advance. A computer algorithm will be written to generate a large number of allocation sequences and to select only those sequences that minimize the imbalance between the two groups of hospitals. One of those sequences will be randomly selected by the computer and will be used to assign hospitals to the control or intervention groups. Both analysis of the baseline data and the allocation procedure will be done by an independent data center (Research Triangle Institute, North Carolina, USA) and their results communicated to the study coordinating unit. Thus, there will be a clear separation between the generator of the intervention allocation and the study coordination [24].

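### The primary hospital-level test does not model the factors that constrain the allocation; where these predict outcome, it is conservative and its intervals are wider than necessary

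*Protocol article*

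**What the plan says.** Under Randomization procedures: "We will use a minimization procedure to assure balance between intervention and control hospitals on five important prognostic variables". The list runs "1) baseline episiotomy and active management rates, 2) residency programs, 3) country (Argentina-Uruguay), 4) hospital size (number of births per year"), with region within the country as the fifth. A computer algorithm generates many allocation sequences, keeps those with the least imbalance, and draws one at random. Under Participating hospitals: "From the 24 hospitals, only 19 will be randomized".

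Under Data analysis, the outcome is first described as a percentage after the intervention: "The outcome variables will be the percentage of primary and secondary outcomes measured during the three months following the end of the intervention". The next sentence moves to ratios: "Mantel Haenszel summary risk ratios combining the individual ratios for each hospital in the intervention group and non-intervention group will be computed". The test follows: "The intervention and non-intervention groups will then be compared at the group level using Student's t-test on the logarithms of the summary risk ratio". No covariate is named. Mixed models on individual data come in addition; the individual data "will be used to explore the potential for confounding of the main effects of the intervention due to imbalances arising from the group randomization".

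Under Outcome measures, all outcomes are also measured for three months before randomization, so each hospital has its own baseline rate.

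**The concern.** When an allocation is forced to balance on a variable that predicts outcome, the difference between arms no longer carries the variation due to that variable. An unadjusted t-test still counts that variation in its standard error. Its true type I error then falls below 5%, its confidence interval is too wide, and it gives up power that an adjusted analysis would keep. The planned mixed models do not address this. Their stated purpose is confounding from imbalance, whereas here the allocation works and the standard error ignores it.

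The article leaves open what the hospital ratio is. A hospital belongs to one arm only, so a ratio within a hospital would most naturally be follow-up over baseline. In that case baseline does enter, but with its slope fixed at 1 on the log scale. That adds noise when baseline and follow-up are weakly correlated. With 19 hospitals, and 17 degrees of freedom in a two-sample test, the baseline rate is the obvious source of extra precision, and it has already been collected.

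**Working it through.** **Inputs from the article.** 19 hospitals randomized; planning SD 15 points; episiotomy 40% to 20%, a 20-point effect; 18 hospitals (9 per arm); significance level 0.05; 80% power.

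**Assumptions.** Two-sided test; 9 v 10 split; normally distributed hospital rates with the same SD at baseline and follow-up; balancing factors other than the baseline rate not prognostic; correlation ρ between a hospital's baseline and follow-up rates equal in both arms. The article gives no ρ, so a range is shown.

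**1. The plan's own figure.** n per arm = 2 × [15 × (1.960 + 0.842) / 20]² = 8.83, rounded up to 9, so 18 hospitals. Normal-approximation power with 9 per arm is 80.7%. The stated sample size is reproduced, as an unadjusted comparison of hospital rates.

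**2. Formula-based power with 9 v 10 hospitals (noncentral t).** The standard error is s × √(1/9 + 1/10) = 0.459 s.
- Post-only: s = 15, standard error 6.89, power 78.1%.
- ANCOVA on the baseline rate: s = 15 × √(1 − ρ²). Power is 77.8 / 81.5 / 88.2 / 96.8% at ρ = 0 / 0.3 / 0.5 / 0.7.
- Change score, as a percentage-scale stand-in for follow-up over baseline: s = 15 × √(2(1 − ρ)). Power is 49.0 / 63.8 / 78.1 / 94.2%.

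**3. Simulation with constrained allocation.** 19 hospitals, five balancing covariates, allocation drawn from the best 5% of 300 candidate sequences, 4,000 runs per setting. Each cell gives type I error, power at 20 points, and mean width of the 95% interval in points.

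| ρ | Post-only t-test | Change-score t-test | ANCOVA on baseline |
|---|---|---|---|
| 0 | 4.8%, 78%, 29 | 1.2%, 47%, 41 | 4.9%, 77%, 28.8 |
| 0.3 | 4.0%, 80%, 29 | 1.9%, 66%, 34 | 4.4%, 82%, 27.6 |
| 0.5 | 2.8%, 80%, 29 | 2.8%, 80%, 29 | 4.9%, 88%, 25.1 |
| 0.7 | 1.4%, 84%, 29 | 3.8%, 96%, 22 | 5.3%, 97%, 20.6 |
| 0.8 | 0.4%, 84%, 29 | 4.4%, 99%, 18 | 5.3%, 99.5%, 17.3 |

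Adjusting for all five covariates instead gives power of 73 / 77 / 85 / 96 / 99%, which is below the post-only test at ρ = 0 and 0.3.

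**4. A stricter balance rule.** Allocation drawn from the best 924 of all 92,378 splits into 9 + 10, with seven covariates, at ρ = 0.3 / 0.5 / 0.7:
- post-only: type I error 3.8 / 2.8 / 0.8%, power 80 / 80 / 85%;
- change score: type I error 1.3 / 2.2 / 3.5%, power 64 / 79 / 95%;
- ANCOVA: type I error about 5%, power 82 / 88 / 97%.

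The pattern does not depend on which of the two rules is used.

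**5. Reading the results.** At ρ = 0.5 ANCOVA gains 88 − 80 = 8 points over either alternative. At 0.7 it gains 97 − 84 = 13 points over post-only and 1 over the change score. At ρ = 0 it loses about 1 point to post-only and gains 77 − 47 = 30 over the change score.

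**The case against.** A reader might infer that the primary test adjusts for none of the balancing factors. The article does not support that for the baseline rate: if the hospital ratio is follow-up over baseline, the baseline rate is already in the test as a denominator. The post-only type I errors and power losses at ρ of 0.7 or more then largely disappear. What remains on that reading is the inefficiency of a fixed slope when ρ is low or moderate.

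A reader might also infer that the trial needs adjustment to reach its planned 80%. It does not on the post-only reading. The sample size was computed for an unadjusted comparison, and simulated unadjusted power is 78-84% (85% at ρ = 0.7 under the stricter rule). The 78.1% in step 2 comes from using the t distribution instead of the normal, not from leaving out covariates. For oxytocin the article already claims power above 95% for a 10-point rise and expects 40 points, so lost power is of little consequence there.

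The size is also uncertain. The article gives neither ρ nor a cut-off for acceptable sequences. An intervention meant to halve episiotomy could weaken ρ in its own arm. The error is in the conservative direction and does not raise the false-positive risk. Covariate lists are often left to an analysis plan, which is not shown here.

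These objections limit the claim without removing it. The article goes beyond silence on covariates: it fixes a covariate-free t-test as the main comparison and gives modelling only an exploratory role. Residency, country, size and region stay outside the test on either reading, and ANCOVA matches or beats both readings, apart from about 1 point at ρ = 0.

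**Conclusion.** The point holds as a matter of efficiency and calibration. The allocation is constrained on variables called prognostic, and the primary test does not model them; the baseline rate enters at most through an undefined ratio. Relative to a baseline-adjusted analysis, the post-only test loses nothing at ρ = 0, about 2 points of power at 0.3, 8 at 0.5 and 13 at 0.7, and its interval stays about 29 points wide where the adjusted one narrows to 25.1 at 0.5 and 20.6 at 0.7. If the ratio is follow-up over baseline, the loss falls at low correlation instead, about 30 points at ρ = 0 and about 16 to 18 at 0.3. Only on that reading, and only at low ρ, does power fall well below 80%.

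The direction is firm if the balancing factors predict outcome, as the protocol says. The size is conditional on ρ and on the assumptions listed in the working, including the percentage-scale approximation to the log ratio. Validity is not threatened. The change should be made because it is nearly free.

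**What to change.** Define the hospital-level outcome as the post-intervention percentage, and remove or define the hospital ratio. Make the primary analysis a hospital-level ANCOVA of that percentage on arm and the hospital's baseline percentage of the same outcome. Do not add all five factors with only 19 hospitals. Support the result with a randomization test over the set of permitted allocations from which the actual one was drawn, which requires keeping that set. Keep the unadjusted t-test as a sensitivity analysis.

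The cost is analysis wording and one degree of freedom. No new data are needed, because the baseline rates are collected before randomization. If baseline proves uncorrelated with outcome, about 1 point of power is lost; a separate beta-binomial simulation with 9 v 9 hospitals gave 71% v 74%, a loss of 3 points.
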